### Description of statistical analyses

The primary endpoint is the proportion of patient consultations for AFI which result in antibiotic prescription. The primary comparison between the treatment arms will be a logistic regression with the treatment assignment as a fixed effect, and the PHC as a random effect. P values (two-sided) below 0.05 are considered significant. A two-sided 95% CI for the OR of being prescribed antibiotics will be calculated.

The primary endpoint (proportion of patients given an antibiotic prescription) will also be investigated by subgroup to assess whether any change in antibiotic prescribing is homogeneous across subgroups. Specifically, intervention effects and appropriate tests for heterogeneity will be calculated in the following predefined subgroups:

Age: younger children aged ≥1 to <5 years, older children aged 5 to <15 years and adults aged ≥15 years.Sex at birth: male or female.Patients with a documented fever or hypothermia at presentation versus patients without.

The secondary endpoints will be analysed in a similar manner to the primary endpoint. A detailed Statistical Analysis Plan will be developed prior to the completion of recruitment for the study.

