## Methods and analysis

### Design

This is a pragmatic, cluster-randomised controlled trial with two study arms consisting of 15 PHCs in the intervention (EDAM-guided clinical management, further details of which are provided below) arm and 15 PHCs in the control (standard care) arm. A PHC will be considered as a cluster, and the assignment of PHCs to arms will be randomly performed by computer. The pragmatism of the study was confirmed using the PRagmatic Explanatory Continuum Indicator Summary−2 tool,^20^ with the majority of the study design domains rated ‘very pragmatic’ (online supplemental information S1).

The rationale for this study design is that any study assessing the potential performance of eCDSAs like EDAM must necessarily be pragmatic and conducted in environments as similar to real-world conditions as possible. Otherwise, in a research-oriented context, healthcare worker prescribing and other management practices may be consciously or unconsciously affected. Furthermore, for policy-makers to consider wide-scale eCDSA implementation, what is most needed is a pragmatic implementation study of its impact in routine care. As such, this study will evaluate the introduction of EDAM into routine care with no research staff routinely present. To minimise disruption and alteration of routine care, a waiver of written patient informed consent was requested from the relevant ethics committees, in accordance with the 2016 WHO/CIOMS International Guidance for Health-related Research Involving Humans. In brief, the 2016 CIOMS Guideline 10 states that in the following circumstances a waiver of informed consent could be applied^21^:

if the research would not be feasible or practicable to carry out without the waiver or modification;if the research has important social value; andif the research poses no more than minimal risks to participants.

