### Sample size calculations

There is scant reliable routinely collected data on antibiotic prescription in the study PHCs. The baseline rate of antibiotic prescription was based on the findings from SEACTN, which includes PHCs where the proposed trial will be run,^12^ where data on patients prescribed antibiotics for AFI have been systematically collected since 2021. In the PHCs participating in this planned interventional study, the mean proportion of acutely febrile patients prescribed antibiotics was approximately 25%. The ICAT cluster-randomised trial, in which the proportion of patient recruited by age group was broadly similar to that seen in SEACTN, showed that the use of CRP rapid tests reduced the antibiotic prescription rate by 36%.^4^ Therefore, it is estimated that EDAM will result in a reduction of antibiotic prescription from 25% to 17.5%.

PHCs participating in SEACTN will also participate in this study if they meet criteria for inclusion. Other PHCs will be selected for inclusion in this study, if required, to make up a total of 15 PHCs in each of the control and intervention arms per country, on the assumption that their antibiotic prescription rates are also broadly similar. The PHCs will be drawn from across three Operational Districts as defined by the Battambang Provincial Health Department, with 10 selected from each operational district. As mentioned previously, each PHC will be treated as a cluster. Given the above, the sample size calculations are based on probabilities of 0.05 and 0.2 for type I and type II errors, respectively, and an intraclass correlation coefficient of 0.025, as is common for cluster randomised trials of this nature.^6 33^ Based on the parameters mentioned previously, with 15 clusters per arm the target number of patients to be recruited per cluster is 152 while assuming a drop-out rate of 10%. In total, therefore, the target number of patients to be recruited is 4560. Sample size calculations were performed in Stata V.18.

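### With 30 PHCs, neither the 5% level nor the 80% power is assured: the stated primary model names no small-sample method or district term, and the sample size rests on a normal reference

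*Protocol article*

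**What the plan says.** In the protocol article, the section Description of statistical analyses sets the primary comparison as a logistic regression with a fixed effect for arm and the "PHC as a random effect. P values (two-sided) below 0.05 are considered significant". It adds that "A two-sided 95% CI for the OR of being prescribed antibiotics will be calculated". Secondary endpoints are to be analysed in a similar way, and a detailed statistical analysis plan is promised before recruitment ends.

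The section Design gives "two study arms consisting of 15 PHCs in the intervention" arm and 15 in the control arm. The section Sample size calculations says that the PHCs were randomised within three operational districts, ten per district. It assumes a fall from 25% to 17.5%, "probabilities of 0.05 and 0.2 for type I and type II errors, respectively", "an intraclass correlation coefficient of 0.025" and 10% dropout. It arrives at 152 patients per PHC and 4,560 in total.

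The article does not name the estimation method, the reference distribution, the degrees of freedom or a district term.

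**The concern.** Treatment varies only between PHCs. The 4,560 patients therefore inform the treatment contrast through 30 cluster values, with about 28 degrees of freedom, or 26 once two district terms are fitted. An ordinary maximum-likelihood fit underestimates the between-PHC variance, and a normal reference ignores the limited degrees of freedom. Both make p values too small.

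Leaving out district works the other way. Stratification balances district differences between the arms, but a model without district counts them as PHC variance, which inflates the standard error.

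At stake are the error rate of the single primary test, the coverage of its interval, and the power claim. The secondary endpoints inherit the same model.

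**Working it through.** **1. The plan's own figure.** The inputs are those of the section Sample size calculations.

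- Individually randomised, pooled-variance normal formula: n = [1.96·√(2 × 0.2125 × 0.7875) + 0.8416·√(0.25 × 0.75 + 0.175 × 0.825)]² / 0.075² = 465.8, so 466 per arm.
- With clustering: 15m = 466 × [1 + (m − 1) × 0.025]. This gives 3.35m = 454.35 and m = 135.6, so 136.
- With dropout: 136 / 0.9 = 151.1, so 152. Then 152 × 30 = 4,560.

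The match is exact, and it uses a normal reference.

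**2. Power with a t reference.** The effective size per arm is 15m / [1 + (m − 1) × 0.025], and the t columns use the noncentral t.

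| Analysed per PHC | Effective n per arm | Normal | t, 28 df | t, 26 df |
|---|---|---|---|---|
| 136 | 466.3 | 80.0% | 77.5% | 77.2% |
| 137 | 467.0 | 80.1% | 77.5% | 77.3% |
| 152 | 477.5 | 81.0% | 78.4% | 78.2% |

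The primary outcome is recorded at presentation, so the number analysed may be nearer 152 than 136.

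**3. Closed-form size of a normal-reference test.**

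- With 28 df: 2P(t₂₈ > 1.96) = 6.0%. Allowing for the maximum-likelihood variance bias (28/30), it is 6.9%.
- With district fitted (26 df, bias 26/30): 8.0%.

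**4. Simulated size.** There were 10,000 trials per scenario with no true effect and a rate of about 25%. Each had 30 PHCs, 5 v 5 in each of three districts. A random-intercept logistic model was fitted by maximum likelihood (15-point adaptive quadrature). The Monte Carlo standard error is about 0.25 points.

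The ICC of 0.025 was read in two ways. On the proportion scale, the logit variance is 0.025 × 0.1875 / 0.1875² = 0.133 (SD 0.365). On the latent scale, it is 0.025 / 0.975 × 3.29 = 0.084 (SD 0.29). District differences and the cluster-size CV are assumptions. ±0.2 logit around 25% means district rates of about 21%, 25% and 29%.

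| Scenario | As written, z | As written, t₂₈ | District added, z | District added, t₂₆ |
|---|---|---|---|---|
| No district difference, 152 | 6.8% | 5.6% | 7.9% | 6.5% |
| Same, 137 | 7.0% | 5.9% | 8.1% | 6.8% |
| Same, 152, latent ICC | 6.3% | 5.1% | 7.2% | 6.0% |
| Same, 152, cluster-size CV 0.3 | 7.1% | 6.0% | 8.2% | 6.8% |
| Districts ±0.1 logit | 6.1% | 5.3% | 7.8% | 6.5% |
| Districts ±0.2 logit | 4.6% | 3.7% | 7.4% | 6.3% |
| Districts ±0.4 logit | 1.8% | 1.3% | 7.3% | 6.1% |

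For the model as written at 152 per PHC, the mean model standard error against the empirical SD was:

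- 0.144 v 0.150 with no district difference
- 0.156 v 0.149 at ±0.2 logit
- 0.188 v 0.150 at ±0.4 logit

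The interval is therefore too narrow in the first case and too wide in the other two.

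With district in the model, replacing z by t on the maximum-likelihood fit still leaves 6.0% to 6.8%, because the variance bias remains. A PHC-level t test adjusted for district (26 df) held 4.5% to 4.9% in a separate run of 4,000 trials.

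**The case against.** The strongest reply is that the article is silent and does not exclude a correction. It names a model class, a threshold and an interval. Maximum likelihood and a Wald z test are assumptions about how the model will be fitted. A degrees-of-freedom method is ordinary content for an analysis plan, which is promised and not shown. A random-effects logistic model on 30 clusters is a recognised analysis. All of this stands: the absence of a named method is not an error in itself, and the size figures are conditional on an uncorrected fit.

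A reader might infer something stronger: that the plan has ruled out a correction, that its test runs at 7% to 8%, and that its interval is too narrow. The document does not support this. For the model as written the range is 6.3% to 7.1%, and only if districts do not differ. Figures up to about 8% need a district term that the article does not list. With omitted district differences of about ±0.2 logit or more, the direction reverses.

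A PHC-level regression of proportions also estimates a risk difference, whereas the article promises an odds ratio. That is a fair limit on one form of the remedy.

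The reply does not reach the sample size. That calculation is in the article, reproduces only with a normal reference among the variants tried, and makes no allowance for 30 clusters.

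**Conclusion.** The concern holds in a limited, conditional form, and it is moderate. The model as written does not secure the stated 5% level or 95% coverage in either direction. An uncorrected fit gave anything from 1.8% to 7.1% across the scenarios tried, depending on district differences that the documents do not report. Adding district while keeping a normal reference moves it to about 7% to 8%, so the two changes belong together.

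The stated error probabilities of 0.05 and 0.2 do not both hold at 152 per PHC. If the 5% level is protected with t on 26 to 28 df, power is about 77% to 78%. If a normal reference is kept for the nominal 80%, the test runs at about 6% to 7% when districts do not differ.

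The power result needs only the plan's own inputs. The size results also assume maximum-likelihood fitting and the district patterns shown.

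**What to change.** For the primary test, include operational district and name a small-sample reference of about 26 df. There are two routes:

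- A mixed logistic model with a small-sample degrees-of-freedom correction, which keeps the odds ratio. The correction must also deal with the variance bias, since a t reference on the maximum-likelihood fit is not enough. Such corrections were not simulated here, so their size should be checked at the plan's values.
- A PHC-level regression of proportions on arm and district, as the primary test or as a pre-specified check. As the primary test it would change the effect measure to a risk difference, and the plan would have to say so.

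Restate power as about 77% to 78%. Settle the method before outcomes are seen by arm.

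**Cost.** This takes a sentence or two in the plan and a slightly lower power figure. If districts do not differ, the interval is about 5% to 8% wider: 2.048 / 1.960 = 1.045 for the t reference alone, and 1.045 × √(30/28) = 1.082 with the variance bias. At 26 df with the same bias factor it is 1.049 × 1.035 = 1.086. If districts differ materially, adjustment offsets this and may narrow the interval. If the analysis plan already names such a method, only the power figure needs restating.

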### Data management

Data will be captured electronically through the EDAM app and submitted to a central server. A data dictionary will be constructed in which all variables are clearly explained. A logbook of patients screened and recruited will also be maintained.

Patients will be assigned a unique composite ID number each time they are enrolled. They will be identified only by their unique ID number on study documents, in data entry and in any electronic databases in order to protect their privacy. The only patient-identifying data entered in the logbooks will be the names of patients, their villages of residence and their telephone numbers, for the purposes of carrying out follow-up. No other identifiers will be collected, and these details will not be entered into any databases held or accessed by the study team. All documents will be stored securely and only accessible by study staff and authorised personnel. Any scientific publications or reports will not identify any individual participant/s by name or initials.

Electronic data will not be modifiable by the healthcare worker after submission, although authorised users, for example, site research staff will be able to do so for data cleaning purposes. Access to the data will be password protected. Direct access will be granted to authorised representatives from the University of Oxford, the study site partners and the respective national ethics committees for monitoring and/or audit of the study to ensure compliance with regulations.

The database and all electronic data will be routinely backed up. In accordance with MORU Standard Operating Procedures, deidentified electronic data will be stored indefinitely on the central server, while paper records will be preserved for 5 years.

Healthcare workers will be trained prior to study commencement on collection of data using the version of the EDAM app relevant to their PHC. Training materials, for example, videos will be uploaded to the tablet devices in case they need to refer to these.

### Data quality assurance

Data validation will be performed to identify errors and thus ensure completeness, validity and data accuracy.

Electronic data checks and field restrictions will prevent errors with extreme values being entered, for instance by having prespecified ranges for vital sign measurements. Further internal checks of the entered data will be done to look for outliers and errors. Additionally, because data will be transmitted in real time or near-real time to the central server, data cleaning will occur prior to the conclusion of the study allowing for earlier detection and correction of errors if necessary.

The study will be conducted in compliance with this protocol, International Conference on Harmonization Guidelines for GCP and any applicable regulatory requirement(s). Staff involved in data collection, interviews, transcription and data coding will be appropriately qualified to perform assigned tasks and will be trained on study procedures prior to start of the study. Monitoring will be overseen by the MORU Clinical Trials Support Group to ensure compliance to the study protocol and applicable guidelines and regulations.

### Safety considerations

The risks of participation are low. First, measurement of oxygen saturation using pulse oximetry is now considered the ‘fifth vital sign’ and is recommended by the WHO when possible in rural LMIC primary care settings,^34^,^36^ therefore its use is not controversial. Second, symptom-based and vital sign-based diagnostic algorithms, such as the Integrated Management of Childhood Illness guideline, are also widely used in clinical practice. Lastly, MORU has previously conducted a large clinical trial on CRP-guided treatment in patients with AFI with extensive patient follow-up, demonstrating that it is effective in reducing antibiotic prescribing and did not adversely affect patient outcomes.^37^ A decision support tool integrating all three would, therefore, not be expected to pose any elevated risk to patient safety. Healthcare workers in the intervention arm are also able to use their discretion if they do not agree with the management recommended by EDAM. Additionally, as an extra safeguard, they will be trained to provide safety netting to all patients they recruit.

Furthermore, in line with the principles guiding data and safety monitoring in pragmatic clinical trials,^38^ an independent Data and Safety Monitoring Board (DSMB) was assembled prior to the commencement of the trial. The DSMB has reviewed the protocol and has access to summary data in real time through the electronic trial dashboard; given the anticipated short duration of this study, no interim analyses will be provided, although it may request additional information if necessary. There are three independent and voting members of this committee, with the chair being medically qualified and one of the other members being a statistician. The DSMB will determine meeting frequency at its first meeting.

Given the pragmatic nature of this simple intervention, remote and on-site monitoring will be undertaken in accordance with a monitoring plan developed prior to study commencement to confirm the quality of the research performed to assess and ensure the robustness of the trial results.

### Status and timeline

This study commenced in late May 2024 and will run until the recruitment target for each cluster is met, which is likely to be approximately 6–9 months.

## Ethics and dissemination

###  Ethical approval

The study sponsor is the University of Oxford, and the protocol has been approved by the Oxford University Tropical Research Ethics Committee (OxTREC, reference 550-23). The protocol has also been approved by the Cambodian National Ethics Committee for Health Research (NECHR, reference 395-NECHR). Permission to carry out the study has been obtained from the local health authority.

Any amendments and modifications will be submitted to the above-mentioned boards for review and approval. No changes in protocol conduct will be implemented until approvals of amendments by all relevant boards are obtained.

### Trial registration

This study has been registered in the International Standard Randomized Controlled Trial Number (ISRCTN) Registry (reference number ISRCTN15157105).^39^

### Dissemination

The results of the study will be published in appropriate peer-reviewed journals. Authorship eligibility will be based on the criteria set by the International Committee of Medical Journal Editors,^40^ with author contributions described using the Contributor Roles Taxonomy.^41^ There are no plans to use professional medical writers in the drafting of the manuscript containing the results of the study.
